## Abstract

**Background:**

Complicated intra-abdominal infections (cIAIs), often caused by multidrug-resistant bacteria such as carbapenem-resistant *A. baumannii* (CRAB) and carbapenem-resistant Enterobacteriaceae (CRE) are a critical challenge in ICUs. Owing to their high mortality and treatment failure rates, there is an urgent need for effective therapies. This trial will compare eravacycline to tigecycline for treating cIAIs in patients in the ICU, aiming to provide a superior treatment option.

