Eravacycline, the world’s first fluorocycline antibacterial agent, is a promising alternative because of its broad-spectrum activity against common MDR bacteria (9). *In vitro* experiments have shown that the activity of eravacycline against *A. baumannii* is 8 times and 2 times greater than those of minocycline and tigecycline, respectively (10). Despite these *in vitro* findings, clinical evidence supporting the use of eravacycline in the treatment of cIAIs, particularly in the context of increasing tigecycline resistance, is lacking. This trial aims to fill this evidence gap by evaluating the clinical efficacy and safety of eravacycline compared with those of tigecycline in patients in the ICU with cIAIs.

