## Statistics

11

This study is a randomized controlled clinical trial. The two groups are the eravacycline group and the tigecycline group, with a ratio of 1:1. All-cause 30-day mortality is the main outcome measure. The researchers plan to use noninferiority tests for the ratio of two propositions to estimate the required sample size, assuming a noninferiority ratio of 2. Owing to the lack of randomized clinical trials in this specific field, sample size estimates were obtained from Xavier Guirao et al.’s observational study on the treatment of intra-abdominal infections with TGC (16). In their study, the all-cause mortality of patients treated with TGC (our control group) was 18.7%. Our previous results revealed that the mortality rate of the eravacycline group (17.7%) was slightly lower than that of the tigecycline group, with an estimated actual ratio of 0.95. The total sample size calculated through PASS (version 15.0.5) is N = 262 cases to perform a unilateral analysis *α*, achieving 80% efficacy at a level of 0.025. Considering a 10% dropout rate, the total number of subjects required for the last two groups is 292, with at least 146 subjects in each group. In light of the considerable variability observed in ICU mortality rates, an interim analysis will be conducted once 50% of the data has been collected. This analysis will facilitate a reassessment of the effect sizes and power of the study. If the initial mortality rates diverge significantly from the anticipated estimates, the sample size will be adjusted accordingly to ensure the integrity and statistical power of the study are maintained.

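### The abstract promises a superior option, but the trial is sized and its hypotheses are written only for noninferiority with a mortality ratio margin of 2

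*Protocol article*

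**What the plan says.** The purpose of the trial is described in several places, and the descriptions differ.

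- **Abstract, Background:** the comparison is presented as "aiming to provide a superior treatment option". The abstract's Methods then give 80% power and an alpha of 0.05, without mentioning noninferiority or a margin.
- **Introduction:** the aim is neutral, namely "evaluating the clinical efficacy and safety of eravacycline compared with those of tigecycline".
- **Section 11, Statistics:** "The researchers plan to use noninferiority tests for the ratio of two propositions to estimate the required sample size", "assuming a noninferiority ratio of 2". The inputs are a tigecycline mortality of 18.7%, an eravacycline mortality of 17.7% and a true ratio of 0.95, at one-sided 0.025 and 80% power. The result is 262 patients, or 292 after 10% dropout. Later in the section, all inference is set as two-sided at 0.05.
- **Section 11.1:** the purpose is to evaluate a difference in efficacy. In symbols, H0 is P1/P2 ≥ R0 and H1 is P1/P2 = R1 < R0. The words beside them run the other way: H0 is described as experimental mortality no higher than control, and H1 as experimental mortality higher. The primary analysis is a Pearson chi-square or Fisher test.

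The article contains no superiority hypothesis, no superiority power and no step from noninferiority to superiority. None of its stated aims uses the word noninferiority, which appears only in the sizing text.

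**The concern.** A reader of the abstract sees a superiority aim next to 80% power and will take the power to belong to that aim. It belongs to a different question: whether eravacycline mortality can be shown to be less than twice that of tigecycline.

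The endpoint is death in ICU patients. At 18.7% control mortality, a ratio margin of 2 corresponds to 2 × 18.7% = 37.4%. If the trial meets its written alternative while the aim keeps its present wording, the result could be reported as having delivered a superior option when nothing about superiority was shown.

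**Working it through.** **Inputs (section 11):** control mortality p2 = 0.187; true ratio 0.95, so p1 = 0.95 × 0.187 = 0.17765 (17.7% as printed); margin R0 = 2; one-sided alpha 0.025; power 80%; 1:1 allocation; 10% dropout.

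**1. Reproducing the plan's 262.** The method is the Farrington–Manning score formula for a ratio of proportions.
- Restricted estimates under p1/p2 = 2 solve 4q² − 3.55165q + 0.36465 = 0, where 3.55165 = 2 + 0.17765 + 1 + 2 × 0.187 and 0.36465 = 0.17765 + 0.187. This gives q2 = 0.1185 and q1 = 0.2370.
- s0 = √[q1(1−q1) + 4q2(1−q2)] = 0.7737.
- s1 = √[p1(1−p1) + 4p2(1−p2)] = 0.8685.
- n per arm = [(1.960 × 0.7737 + 0.8416 × 0.8685) / (2 × 0.187 − 0.17765)]² = (2.2473 / 0.19635)² = 131.0.
- Total 2 × 131 = 262; 262 / 0.9 = 291.1, rounded up to 292.

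Both stated figures match, so the sample size is a noninferiority sample size. Exact binomial enumeration of the score test gives 80.6% power at 131 per arm and ratio 0.95.

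**2. Superiority power at the plan's rates.** This uses the pooled two-sided 0.05 test at 17.7% v 18.7%, with mean rate 0.182.
- Null SD √(2 × 0.182 × 0.818) = 0.5457; alternative SD √(0.177 × 0.823 + 0.187 × 0.813) = 0.5456.
- 131 per arm: z = (0.010 × √131 − 1.960 × 0.5457) / 0.5456 = −1.750, power 4.0%.
- 146 per arm: z = −1.739, power 4.1%.
- With the ratio taken as exactly 0.95, the figures are 3.9% and 4.0%.
- Patients for 80% power: [(1.960 × 0.5457 + 0.8416 × 0.5456) / 0.010]² = 23,369.01 per arm, rounded up to 23,370, or 46,740 in total before dropout. With the ratio at exactly 0.95 the total is 53,538.
- With 131 per arm, 80% superiority power needs an eravacycline mortality of about 7% (7.1% gives 80.3%, 7.2% gives 79.5%), a ratio of about 0.38.

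**3. What a noninferiority pass can look like.** This assumes that the margin decides success. The expected control deaths are 131 × 0.187 = 24.5; 24 is used here.

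| Deaths of 131, eravacycline v tigecycline | Observed ratio | Score z against ratio 2 | Upper 95% limit (log ratio) | Noninferior? |
|---|---|---|---|---|
| 29 v 24 (22.1% v 18.3%) | 1.21 | −2.05 | 1.96 | yes |
| 30 v 24 | 1.25 | −1.93 | 2.02 | no |

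For the first row, the log-ratio SE is √(1/29 − 1/131 + 1/24 − 1/131) = 0.2467, and exp[ln(29/24) + 1.960 × 0.2467] = 1.96. With 146 per arm, 34 v 27 deaths (ratio 1.26) would still pass.

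By exact enumeration at 131 per arm, noninferiority is met together with more observed eravacycline deaths in 19.7% of trials at ratio 0.95, and in 23.0% if mortality is equal.

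**The case against.** **The phrase is loose motivation in the abstract.** It names no endpoint, and the Introduction states the aim neutrally. The case for a better option in the Discussion also rests on resistance and tolerability. This is fair, and it limits the weight of the point. It does not remove it, because neither the Introduction nor section 11.1 names noninferiority as the aim either.

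**A reader might infer that the trial cannot show superiority at all.** The documents do not support that. Sections 11 and 11.1 plan a two-sided 0.05 Pearson or Fisher test of mortality, and that test could detect a very large benefit. What stands is that the trial is not designed or powered for it. The same test takes no account of the margin, so it cannot deliver the noninferiority conclusion either.

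**A reader might also treat passing with more deaths as a fault in itself.** It is a property of any noninferiority design; a ratio margin of 2 makes the allowance wide. The death counts above also assume a score test or confidence interval that section 11.1 does not name. Under the planned Pearson test, 29 v 24 is simply a nonsignificant difference (z about 0.8).

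**The article claims no superiority power.** That is correct. The 4% and 46,740 show the distance between the abstract's wording and the design; they do not show an error in the sample size.

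**A noninferiority-then-superiority sequence is optional and often left to the analysis plan.** Its absence alone is no fault. It matters here because the abstract uses the word superior.

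**Conclusion.** The point holds in this form: the abstract's superiority aim does not match a trial sized, and formally stated in symbols, for noninferiority on 30-day mortality with a ratio margin of 2. The 262 and 292 are correct for that purpose. Superiority power at the plan's own rates is about 4%, and meeting H1 would exclude only a doubling of mortality or worse.

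The power figure rests on the stated 17.7% and 18.7% and on 131 to 146 analysed patients per arm; a much larger true benefit would raise it. The example of 29 v 24 deaths rests on the margin, applied through a score test or ratio confidence interval, being the success rule. That rule is inferred from section 11 and the symbols in section 11.1.

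The change is worth making before results are known, because it settles what the trial may conclude. It goes beyond the abstract's wording, since section 11.1 pairs noninferiority symbols with reversed verbal descriptions and a test that ignores the margin.

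**What to change.** 1. In the abstract and section 11.1, state the aim as showing that eravacycline is noninferior to tigecycline on all-cause 30-day mortality, with a ratio margin of 2.
2. Correct the verbal descriptions in section 11.1 to match the symbols: H0, eravacycline mortality is at least twice that of tigecycline; H1, it is less than twice.
3. Base the primary conclusion on the two-sided 95% confidence interval for the mortality ratio, in place of the Pearson or Fisher test. Noninferiority is concluded if the upper limit is below 2. Only then is superiority examined, and it is concluded if the upper limit is below 1.
4. Use the word superior only if the second step succeeds.

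**Cost:** no added patients and a more modest headline aim. The second step spends no alpha of its own, because it is tested only after the first succeeds. The sequence does not settle how the interim analysis at 50% of the data, or having mortality primary in both the clinically and the microbiologically evaluable populations, affects the error rate. The plan should name the population that governs each step. If superiority is the true aim, 262 patients are far too few at the planned rates.

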**Ethics and communication:**

This trial was approved by the Ethics Committee of Ansteel Group General Hospital. The communication plan includes presentations at scientific conferences, scientific publications, and presentations to the public through nonprofessional media.

**Clinical trial registration:**

https://clinicaltrials.gov/, ChiCTR2300078646.

## Introduction

1

Complicated intra-abdominal infections (cIAIs) pose a significant challenge in the field of critical care medicine, particularly because of the involvement of multidrug-resistant (MDR) pathogens. Carbapenem-resistant organisms (CROs), a subset of MDR bacteria commonly associated with cIAIs, are increasingly recognized for their high incidence, strong resistance profiles, high treatment failure rates, and high mortality rates (1). These bacteria, including carbapenem-resistant *A. baumannii* (CRAB) and carbapenem-resistant Enterobacteriaceae (CRE), had alarming detection rates of 71.2–71.9% and 22.6–24.2%, respectively, in the 2022 CHINET China bacterial resistance monitoring report (2). These incidences highlight the severity of drug resistance issues in recent years.

The clinical outcomes associated with cIAIs are notably poor, often leading to increased ICU occupancy rates, prolonged hospital stays, and a significantly increased mortality rate (3–5). The economic burden of such infections is substantial, with CRE alone causing annual losses of $1.4 billion to hospitals, $800 million to third-party payers, and $2.8 billion to society in the United States (6). Given the profound impact of cIAIs on patient prognosis and healthcare systems, there is an urgent need for effective treatment strategies.

The current therapeutic landscape for MDR bacterial infections, including those complicated with cIAIs, is limited and inadequate. The high initial treatment failure rate of 81.3% for MDR bacterial infections underscores the urgency for new treatment options (7). Tigecycline, once considered a last-resort antibiotic, is now facing a global increase in resistance, with over 50% of multidrug-resistant *A. baumannii* demonstrating heterogeneous resistance to this drug (8).

Eravacycline, the world’s first fluorocycline antibacterial agent, is a promising alternative because of its broad-spectrum activity against common MDR bacteria (9). *In vitro* experiments have shown that the activity of eravacycline against *A. baumannii* is 8 times and 2 times greater than those of minocycline and tigecycline, respectively (10). Despite these *in vitro* findings, clinical evidence supporting the use of eravacycline in the treatment of cIAIs, particularly in the context of increasing tigecycline resistance, is lacking. This trial aims to fill this evidence gap by evaluating the clinical efficacy and safety of eravacycline compared with those of tigecycline in patients in the ICU with cIAIs.

## Study design

2

This study is a multicenter, randomized, single-blind, tigecycline-controlled study involving 5 centers/hospitals. The trial was fully approved by the Ethics Committee of Ansteel Group General Hospital [(2023) Ethics Review No. (14)] and was registered in the Chinese Clinical Trial Registry^1^ with the listed primary and secondary endpoints. This study will be conducted in accordance with the clinical trial protocol (and any revisions), the Declaration of Helsinki (current revision), the international guidelines for the management of intra-abdominal infections, and the Chinese expert consensus (11, 12). The research design is shown in Figure 1.

**Figure 1 fig1:**
[figure not shown]
Flow chart. ICU, intensive care unit; cIAI, complicated intra-abdominal infection.

## Patient selection

4

According to the guidelines, cIAI is defined as an infection that breaks through the primary organ affected and enters the abdominal cavity, causing peritonitis or an abdominal abscess (13). In accordance with the inclusion and exclusion criteria, eligible patients will be registered and randomly assigned to receive intravenous infusions of either eravacycline or tigecycline.

### Inclusion criteria

4.1

1. ICU inpatients with cIAI; 2. Patients are 18 to 85 years old, without sex restrictions; 3. Patients are transferred to the ICU after surgery, with confirmation of an intra-abdominal infection (involving pus in the abdominal cavity) with peritonitis; 4. confirmation of infection through surgical intervention within 24 h after admission to the ICU: evidence of a systemic inflammatory response, consistent with physical examination results of intra-abdominal infection, and supportive imaging findings of intra-abdominal infection; 5. patients whose infected lesions have been effectively removed or drained or who do not require surgical intervention; and 6. the patient or their authorized person fully understands the purpose and significance of the trial, voluntarily participates and signs an informed consent form containing contact information.

### Exclusion criteria

4.2

Patients who are known to have allergies to any excipients containing eravacycline, tigecycline, tetracycline, or investigational drug formulations;Patients with intra-abdominal lesions that are unlikely to have infectious primary causes, such as inflammatory bowel disease, liver abscess, abdominal wall abscess, intestinal obstruction without perforation, or ischemic bowel without perforation;Patients with intra-abdominal infections suspected to be caused by fungi, parasites, viruses, or pulmonary tuberculosis, except in cases of upper intestinal perforation where empirical coverage of fungi is often given, will not be excluded;The exclusion criteria related to antibiotics are as follows: a. within 72 h prior to randomization, effective antimicrobial therapy was used for >24 h [however, patients with clear baseline pathogens and treatment failure after antibiotic treatment for at least 72 h may be enrolled]; b. cases in which cIAI is known to be caused by a pathogen resistant to one of the investigational drugs; c. patients who receive treatment for the current infection with investigational drugs or similar drugs; or d. in addition to research drugs, it is also necessary to use nonresearch antibacterial drugs in combination;An anticipated need for systemic antibiotic treatments lasting more than 14 days;Obvious liver disease, liver function damage (Child–Pugh C grade), or possible signs of liver disease and/or abnormal laboratory test results: a. ALT or AST > 5xULN; b. total bilirubin>3xULN;Patients with congenital or acquired immunodeficiency diseases, those who have received organ transplantation within the previous year of enrollment, or those who have received immunosuppressive drug treatment within 30 days before enrollment;Patients who are within 7 days prior to randomization or who are expected to use potent CYP3A inducers, such as phenytoin sodium, rifampicin, or carbamazepine, during the study period;Patients with systemic malignant tumors that require chemotherapy, immunotherapy, radiation therapy, or antitumor treatment within the 3 months prior to total organic compound (TOC) visits;Pregnant women, lactating women, or those with a fertility plan within 2 weeks after the end of the study;Patients who have participated in clinical trials of other drugs or medical devices within 1 month prior to screening;Patients who are expected to have a survival time or treatment intention of less than 6– to 8 weeks; and.Patients who, as determined by the researchers, do not meet the criteria for inclusion in clinical trials for various reasons, such as concomitant brain herniation, acute myocardial infarction, pulmonary embolism, or ECMO treatment.

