
### Criteria for early withdrawal from treatment

4.3

Early withdrawal from treatment refers to withdrawal from the study treatment before the completion of the treatment course. Patients who withdraw from treatment early are not considered withdrawn from the study early and should continue to complete the follow-up visit process. The study will employ an intention-to-treat analysis, which includes all patients who were initially randomized to receive the study drug, regardless of whether they completed the full course of treatment. This approach ensures that the analysis reflects the provided treatment options’ real-world effectiveness. The criteria for early withdrawal from treatment are as follows:

The patient or their authorized person requests to withdraw from treatment;Patients whose conditions worsen or do not improve after 72 h of continuous use of the investigational drug and who have been determined by the researcher to no longer benefit from continued use of the investigational drug;After the investigational drug is applied, if the sample culture strain is resistant to the drug, the clinical efficacy is evaluated by the researcher as persistent or progressive;Individuals who experience intolerable adverse events/serious adverse events and for whom it has been determined by the researcher that continuing to use the investigational drug would pose a greater risk to the patient than its benefits;Cases in which protocol violations occur, such as receiving other effective antimicrobial treatments (excluding those specified in the protocol) or other concomitant medications prohibited by this protocol during the study period, which, in the judgment of the researcher, might seriously affect the elimination, metabolism, or efficacy evaluation of the investigational drug;Other situations that require early withdrawal from treatment.

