## Population definition

7

The microbiologic modified intention to treat (mITT) population will include all patients with a confirmed diagnosis of complex abdominal infections (cIAIs) and positive infection source samples and/or blood sample cultures at baseline [excluding pathogens not expected to respond to either trial drug, such as nonfermenting gram-negative bacilli (e.g., *P. aeruginosa*, fungi, or mycobacteria)]. The mITT population will be used for demographic and baseline purposes.Clinical evaluation (CE) population: In the mITT population, researchers will follow the requirements of important components of the study protocol [such as cultivating baseline pathogenic gram-negative pathogens (reported in infection source samples and/or blood samples)], excluding those patients with pathogens (*P. aeruginosa*) who do not respond as expected to the investigational drug. This population will be used for clinical efficacy and all-cause mortality analysis.Microbiologically evaluable (ME) population: In the mITT population, individuals who have completed the study in accordance with important components of the study protocol and obtained baseline pathogenic gram-negative pathogens (reported in infection sources and/or blood samples) are expected to respond to the investigational drug. This population will be used for clinical efficacy, microbiological efficacy, comprehensive efficacy, and all-cause mortality analyses.Safety analysis (SS) population: Patients who have received at least one dose of the investigational drug during the clinical study period. The safety analysis population will be used for the analysis of safety data.

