## Effectiveness evaluation

8

The primary efficacy end point is the all-cause 30-day mortality of patients in clinically evaluable and microbiologically evaluable populations.

The secondary efficacy endpoints are as follows: (1) the proportion of patients with a total response (composite endpoint consisting of clinical cure and microbiological response) in the clinically evaluable population at the end of treatment (days 5–14) and the test of cure visits (days 12 ± 2); (2) the proportion of total responsive patients in the microbiome-evaluable population at the end of treatment and the test of cure visits; (3) the proportion of microbiologically evaluable patients in the population with a total response to each pathogenic bacterium at the end of treatment and the test of cure visits; (4) the total response proportion of patients with drug-resistant bacterial infections in the microbiome-evaluable population at the end of treatment and the test of cure visits; (5) ICU hospitalization time and expenses; (6) quality of life outcomes or functioning after ICU discharge as assessed by application of the EuroQol-5D and Barthel Index scales; (7) changes in Sequential Organ Failure Assessment (SOFA) scores, reflecting the impact of the treatment on organ dysfunction over time; and (8) time to clinical improvement, measured from the start of treatment until the first observation of significant improvement in clinical status.

Given the variable susceptibility of MDR pathogens to tetracyclines, our study protocol will include analyses stratified by bacterial species. Specifically, subgroup analyses will be conducted for CRAB and CRE to gain a deeper understanding of the comparative efficacy of eravacycline versus tigecycline.

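### The trial is introduced as evidence for rising tigecycline resistance but excludes known resistance, and its drug-resistant endpoint uses a population that resistant failures can leave

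*Protocol article*

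**What the plan says.** **Purpose.** The Introduction (section 1) says that clinical evidence for eravacycline in cIAI, "particularly in the context of increasing tigecycline resistance, is lacking. This trial aims to fill this evidence gap".

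**Entry.** Item b of the antibiotic-related exclusions in section 4.2 bars "cases in which cIAI is known to be caused by a pathogen resistant to one of the investigational drugs". It covers both study drugs, so a known tigecycline-resistant infection is ineligible even when the isolate is susceptible to eravacycline.

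**During treatment.** One of the criteria in section 4.3 for stopping study treatment early reads: "After the investigational drug is applied, if the sample culture strain is resistant to the drug", combined with infection that the researcher judges persistent or progressive. The same section keeps these patients in follow-up and announces an intention-to-treat analysis. Section 6 makes resistance testing routine for both drugs and provides for crossover once resistance is found.

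**Analysis.** Section 7 limits ME to mITT patients who completed the study in line with the protocol's important components and whose baseline gram-negative pathogens "are expected to respond to the investigational drug". It assigns mITT to demographic and baseline description. In section 8, ME is one of the two populations for the primary mortality endpoint and the only population for endpoint 4: "the total response proportion of patients with drug-resistant bacterial infections in the microbiome-evaluable population".

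**The concern.** There are two linked problems.

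First, the rationale is wider than the population. A reader of the results would take them to bear on tigecycline resistance, but patients with known resistance cannot enter. Similar mortality in the two arms would describe infections not known at entry to be resistant to either drug.

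Second, the endpoint closest to the rationale is measured in a set whose membership can depend on what happens after randomisation. A patient found resistant who does badly may stop study treatment or cross over, and may then not count as having completed according to protocol. The pathogen condition for ME is also written in terms of a single study drug. If a site reads that as the drug received, the same isolate may qualify in one arm and not in the other. The endpoint 4 comparison, and the ME mortality comparison with it, would then no longer be a comparison of randomised groups.

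**Working it through.** **1. The plan's own figure, and whether this point touches it.** Section 11 gives control mortality p2 = 0.187, true ratio 0.95 (so p1 = 0.95 × 0.187 = 0.17765), non-inferiority ratio R0 = 2, one-sided α = 0.025, power 80% and 10% dropout. The score test for a ratio of proportions gives

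n per arm = [(z₀.₉₇₅·s0 + z₀.₈₀·s1) / (R0·p2 − p1)]²

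- Rates constrained to p1 = 2·p2: 0.2370 and 0.1185.
- s0 = √(0.2370·0.7630 + 4·0.1185·0.8815) ≈ 0.774.
- s1 = √(0.17765·0.82235 + 4·0.187·0.813) ≈ 0.868.
- Denominator: 0.374 − 0.17765 = 0.19635.
- n = 131 per arm, total 262. With dropout, 262/0.9 = 291.1, rounded up to 292.

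Both stated totals are reproduced. No input involves resistance status or endpoint 4, so the sample size is unaffected.

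**2. Purpose against entry.** The Introduction singles out tigecycline resistance. Section 4.2 admits no patient with known resistance to either drug. Direct evidence can come only from patients whose resistance is recognised after randomisation.

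**3. How much evidence that could be.** The article gives no share of such patients. Purely as an illustration, assume a share of the 292 enrolled and apply the trial's own ratio-2 mortality test at the trial's own rates, with power = Φ{[(R0·p2 − p1)·√n − z₀.₉₇₅·s0] / s1} and n per arm:

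| Assumed share | Patients (both arms) | Power in that subgroup |
|---|---|---|
| 2% | about 6 | about 9% |
| 5% | about 15 | about 13% |
| 10% | about 29 | about 19% |
| 20% | about 58 | about 30% |

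The normal approximation is rough at these sizes, and mortality in resistant infection need not equal the planning rates. The table shows only that the information would be thin across a wide range.

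**4. Route to endpoint 4 for a patient found resistant.** The patient enters because resistance was not known. Routine testing then identifies it. If infection persists or progresses, the criterion in section 4.3 is met; crossover under section 6 is also possible. Follow-up continues, but ME additionally asks for protocol-conforming completion and a qualifying pathogen. Either condition can remove the patient from ME, and endpoint 4 names no other set.

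**5. Three readings of the ME pathogen condition.** Section 7 does not mention resistance in the ME definition, so the reading is open:

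| Reading | Tigecycline-resistant, eravacycline-susceptible isolate | Eravacycline-resistant, tigecycline-susceptible isolate |
|---|---|---|
| By kind of organism (as with *P. aeruginosa*) | Stays in both arms | Stays in both arms |
| By susceptibility to both drugs | Leaves in both arms | Leaves in both arms |
| By susceptibility to the drug received | Stays in eravacycline arm, leaves in tigecycline arm | Leaves in eravacycline arm, stays in tigecycline arm |

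Only the third differs by arm. The completion requirement operates under all three.

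**6. Effect on the endpoint.** Let an arm have r patients with drug-resistant infection, of whom f fail, and let k of those failures leave ME. The observed response proportion is (r − f)/(r − k), compared with (r − f)/r if nobody left. It is too high whenever k > 0 and some patients respond. The between-arm comparison is distorted according to how k compares with r in each arm, and the article fixes neither value.

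**The case against.** The case on the other side is substantial.

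- **The operative aim is general.** The sentence that states it goes on: "This trial aims to fill this evidence gap by evaluating the clinical efficacy and safety of eravacycline compared with those of tigecycline", in ICU patients with cIAI. Tigecycline resistance is context. A reader might infer that the trial cannot meet its objective. The document does not support that, because no hypothesis is set in tigecycline-resistant infection.
- **Only known resistance is excluded**, and the exclusion itself is not an error.
- **Resistance alone does not end study treatment.** A reader might infer that it does, but the criterion also needs persistent or progressive infection. Those patients stay in follow-up and in the announced intention-to-treat analysis.
- **Removal from ME is an inference.** The organisms that section 7 names as not expected to respond are kinds of organism. A reader might conclude that ME will hold no tigecycline-resistant isolate in the tigecycline arm. Under the first reading in the table it would.
- **The singular wording may be generic.** The safety population uses the same singular for both arms, and mITT refers to either drug.
- **Endpoint 4 concerns drug resistance in general**, and CRAB and CRE subgroups are planned.
- **The figure of over 50%** in the Introduction is heterogeneous resistance among multidrug-resistant *A. baumannii*. It is not the share of trial patients affected.

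All of this limits the point. It does not remove it. The intention-to-treat sentence does not change the population to which section 8 ties endpoint 4. CRAB and CRE are defined by carbapenem resistance, so those subgroups do not by themselves address tigecycline resistance. The completion requirement in ME can select on outcome whichever pathogen reading is used.

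**Conclusion.** The point holds in a limited form. The Introduction promises more on tigecycline resistance than the eligible population can deliver: the trial can give little direct evidence on tigecycline-resistant cIAI, although its general comparison in ICU patients remains answerable. Endpoint 4 rests on a set from which resistant patients who fail, stop study treatment or cross over can disappear. That this can happen follows from the wording of ME. That it will happen, and that it will differ by arm, depends on how sites apply an unclear condition.

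A reader might infer that the selection deletes tigecycline failures and so flatters tigecycline. The document does not fix the direction, because isolates resistant only to eravacycline would be handled in the mirror-image way.

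The number of patients affected cannot be derived from the article, and the sample size does not change. This is an inexpensive improvement worth making; it does not invalidate the trial.

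**What to change.** Eligibility, treatment withdrawal and crossover rules stay as they are.

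1. **Aim and conclusion.** State that they apply to cIAI not known at entry to be resistant to either study drug, and present tigecycline resistance as background only.
2. **Endpoint 4.** Make the mITT population, analysed as randomised, the main analysis set. Define resistance from the baseline isolate, tested against both drugs in both arms. Keep the ME analysis as supportive. Section 7 must then give mITT a use beyond baseline description. The Statistics section already counts missing response as failure in the microbiological intention-to-treat population.
3. **Pathogen condition.** State that in mITT, CE and ME it is judged from the baseline organism by a single rule that is identical in both arms and never depends on the assigned drug. mITT must be covered because it carries its own pathogen filter.

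The cost is wording in sections 1, 7 and 8. Section 6 already plans routine resistance testing for both drugs, so no new laboratory work is foreseen. The price is a narrower claim and an endpoint 4 analysis that includes patients who did not adhere to the protocol.
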